### Randomization, allocation, and implementation procedures

Central randomization will be conducted by INTELLIGENCE FUTURE Soft Co., Ltd. (Tianjin, China). A random sequence will be generated with SAS 9.2 (SAS Institute, Inc., Cary, NC, USA) by an independent statistician who is not involved in the study, and the sequence will be stored in a central randomization system (interactive web response (IWR) system). Allocation will adopt a stratified random method. Stratified block randomization will be carried out by third party statisticians who will be not involved in any other part of the trial. The patients will be stratified based on the two different centers and randomly assigned to the Ma’s bamboo-based medicinal moxibustion group and the acupuncture group in a 1:1 ratio. The Ma’s bamboo-based medicinal moxibustion group will receive Ma’s bamboo-based medicinal moxibustion therapy. Regular acupuncture therapy will be performed on the acupuncture group. There are two investigators at each center (referred to as A and B). Investigator A will log in to the central randomization system on the computer and be responsible for inputting baseline data of patients, waiting for the system to assign random numbers and grouping, but he will not know the details of grouping and will not participate in treatment. Investigator B is responsible for performing treatment according to the grouping. Due to the nature of the intervention, it is not feasible to conceal the assignment from Investigator B and the patient, but Investigator B will not be permitted to disclose any information about his treatment to Investigator A or the patient. At each visit, A is responsible for collecting data and entering the data in the electronic data capture (EDC) system. The therapist and the data collector are separate. Statisticians are responsible for data processing and are not aware of the grouping until the end of the trial.

### Blinding

In this trial, patients and therapists will not be blinded due to the uniqueness of the two therapies. Investigators and statisticians will be blinded. Treatment, data collection, and data analysis will be conducted by trained practitioners, data collectors, and statisticians, respectively, all blinded to one another in order to ensure the reliability of the results.

The conditions for unblinding are (1) infection or other adverse events, and these patients will be withdrawn from the trial or (2) the end of the trial and data analysis.

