### Study objectives

The objective of this randomized controlled trial is to evaluate the efficacy and safety of Ma’s bamboo-based medicinal moxibustion therapy in the treatment of patients with LDH low back pain. The specific objectives are (1) to evaluate the effectiveness of Ma’s bamboo-based medicinal moxibustion therapy in improving pain, lumbar dysfunction, daily living ability, and regulating of serum β-endorphin (β-EP) and serum substance P (SP) content in patients with LDH low back pain and (2) to evaluate the safety of this therapy by recording blood routine, liver and kidney function, electrocardiogram results, and the number, nature, and severity of adverse events.

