#### Drop out criteria

Patients who meet any of the following criteria will be withdrawn:Occurrence of severe adverse eventsOther treatments received that could affect the outcomeVoluntary withdrawal for any reason

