### Safety monitoring

Possible adverse events during Ma’s bamboo-based medicinal moxibustion treatment include itching, scald, redness, blister, and infection. Fainting, sticking of needle, hematoma, subcutaneous hematoma, and bleeding might occur during acupuncture treatment. Therapists and subjects are informed to actively report any adverse events during the study. Researchers will track the results of safety evaluation indexes (routine blood test, liver and kidney function, ECG) before and after treatment in a timely manner, and confirm the occurrence of adverse events. Any adverse events that occur during the trial will be recorded in a CRF by researchers and patients will be treated as soon as possible. Patients may choose to withdraw from the trial due to any adverse events. The sponsor and the data management company INTELLIGENCE FUTURE will monitor the implementation of the trial protocol and filling of CRFs.

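### The Blinding section ties withdrawal to adverse events of any severity, in conflict with the Drop out criteria and Safety monitoring sections

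*Protocol article*

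**What the plan says.** Three sections of the protocol article deal with what happens to a patient who has an adverse event.

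- **Blinding.** Two conditions for unblinding are listed. The second is the end of the trial and its analysis. The first is "infection or other adverse events, and these patients will be withdrawn from the trial". No severity, seriousness or relatedness limit is attached. The same section says that patients and therapists are not blinded, while investigators and statisticians are.
- **Drop out criteria.** The section opens with "Patients who meet any of the following criteria will be withdrawn" and lists three criteria: a severe adverse event, another treatment that could affect the outcome, and voluntary withdrawal. Severe events are the only adverse-event criterion.
- **Safety monitoring.** Any adverse event "will be recorded in a CRF by researchers and patients will be treated as soon as possible". Withdrawal is optional: "Patients may choose to withdraw from the trial due to any adverse events". The possible events listed for moxibustion are "itching, scald, redness, blister, and infection". For acupuncture the section says: "Fainting, sticking of needle, hematoma, subcutaneous hematoma, and bleeding might occur during acupuncture treatment".

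The Study objectives section includes "the number, nature, and severity of adverse events" in the safety objective. Under Interventions, treatment is completed within 13 days and assessments fall on days 7, 14 and 28. The Abstract places the blood tests and ECG at baseline and after the end of treatment.

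**The concern.** The Blinding section contains a withdrawal rule that the section devoted to withdrawal does not. Its trigger is wider (any adverse event rather than a severe one), and its wording makes withdrawal compulsory where the Safety monitoring section makes it optional. A site has no text telling it which rule prevails.

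If the Blinding rule were followed as written, participation would end because of a reaction that the treatment itself can cause, and the expected reactions are not the same in the two arms. An event during the treatment period would put the day 14 and day 28 VAS at risk, together with the only post-baseline laboratory and ECG assessment. Removing a patient at a first event could also cut short the record of later events, which belongs to the safety objective. Losses of this kind are unwelcome in any trial. They are particularly so in a non-inferiority comparison under intention to treat, which depends on complete outcomes in both arms.

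The unblinding itself has little clinical purpose, since the therapist and the patient already know the treatment. The roles still blinded are the investigator who collects the data and the statistician.

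**Working it through.** The point is textual, so the main check is to apply each section to the same patient: one with non-severe redness after moxibustion, or a small hematoma after acupuncture.

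| Section | Trigger | Consequence for this patient |
|---|---|---|
| Blinding | Infection or any other adverse event | Ground for unblinding, then withdrawn |
| Drop out criteria | Severe adverse event | Stays in |
| Safety monitoring | Any adverse event | Recorded and treated; may choose to leave |

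The last two rows are compatible: a patient with a non-severe event stays unless he or she decides otherwise, and voluntary withdrawal is itself one of the drop-out criteria. The first row fits neither.

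**Does a narrower reading remove the conflict?** The Blinding text can be read so that withdrawal applies only to patients whose code is actually broken. Fewer patients are then affected. The ground for breaking the code is still any adverse event, however, and withdrawal then follows automatically. Code-breaking is not among the drop-out criteria. The conflict shrinks but remains.

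**Scale against the planned loss.** Inputs from Sample size calculation: 140 per arm required, 10% loss, 156 per arm recruited.

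- The plan's own inflation reproduces: 140 / (1 − 0.10) = 155.6, rounded up to 156.
- Allowance: 156 − 140 = 16 patients per arm, and 16 / 156 = 10.3%.
- If every patient with any adverse event were withdrawn *and* gave no usable data, 16 such patients in an arm would use up its allowance. Both conditions are assumptions; the documents give no event rates.

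**Is power at stake?** Inputs: SD 2.0, margin 0.78, one-sided 0.05 (Sample size calculation); true difference 0 (assumed). With n per arm, SE = 2.0 × √(2/n) and power = Φ(0.78/SE − 1.645).

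- n = 140: SE = 0.239, power = Φ(3.263 − 1.645) = 0.947.
- Loss of twice the allowance, n = 156 − 32 = 124: SE = 0.254, power = Φ(3.071 − 1.645) = 0.923.

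At the stated significance level, even double the planned loss leaves power above the 90% target. (That 140 per arm gives more than 90% at the stated inputs is a separate matter.)

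**The case against.** The strongest reply is that the three sections serve different purposes. One lists drop-out criteria, one says when the code may be broken, and one covers the handling of events and the patient's right to leave. The Blinding section does not say that every adverse event must lead to unblinding. The choice given to patients under Safety monitoring would mean nothing if every event forced withdrawal. A sensible site reading all three would probably not remove a patient for redness. In addition, the Adherence section has withdrawn cases followed up by telephone or at home, and the Statistical analysis section specifies intention to treat with linear mixed models for missing data.

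Much of this stands, and it rules out several stronger readings that a reader might infer:

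- *That every adverse event certainly means removal.* The text permits this reading but does not compel it.
- *That withdrawal means no further data.* The article does not say so, and planned follow-up points the other way. It does not say, though, that VAS, blood tests or ECG are obtained in that follow-up, and a model does not replace observed outcomes.
- *That an abnormal end-of-treatment test would remove the patient before day 28.* Researchers do use the tests "before and after treatment in a timely manner, and confirm the occurrence of adverse events", but the inference also needs the result to be classed as an event, the code to be broken, and the day 28 visit to be dropped. None of these steps is stated.
- *That moxibustion would lose more patients because infection is listed only for that arm.* Both lists are given as possible events, neither is presented as complete, and the Blinding rule covers other events in both arms.

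The reply does not reconcile the wording. This is not a detail that a condensed article has left out. It is a rule the article states and then contradicts twice.

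**Conclusion.** The inconsistency holds. The Blinding section attaches unblinding and withdrawal to adverse events without a severity limit, against a severe-only rule in Drop out criteria and a patient-choice rule in Safety monitoring. Followed literally, it risks avoidable treatment-related loss of VAS and safety data, from reactions that differ in kind between arms.

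The size is unknown. Without event rates, neither the amount nor the direction of any bias can be derived, and none is claimed. Loss of power is not the issue under the assumptions used above. The comparison with 16 patients per arm gives scale only, because it assumes that every affected patient is withdrawn and contributes nothing further. The planned follow-up and analysis mitigate the risk in part. The matter is worth correcting because the rule is operative, sites need one instruction, and the correction is simple.

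**What to change.** In the Blinding section:

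1. Delete the clause that withdraws these patients.
2. Limit unblinding before the end of the trial to severe adverse events in which someone managing the event needs to know the arm and does not already know it.

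Then let Drop out criteria and Safety monitoring alone govern withdrawal, and say so in one sentence. Patients with non-severe events stay in the trial and keep the scheduled VAS assessments on days 7, 14 and 28 and the end-of-treatment safety tests, unless they choose to withdraw. The rule for severe events in Drop out criteria is left as it is.

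The cost is a wording amendment, with no new visits or measurements. Under Protocol amendments it may count as a significant change needing approval from the ethics committee and the project leader. Since the article reports the trial as recruiting, both centers would also have to be told of the single rule.

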### Interventions

All treatments will conduct in the outpatient treatment rooms of the two centers. The therapists will not be involved in the other parts of the trial. The treatments will be performed every day, for a total of 12 treatments. All the treatments will be completed within 13 days. The assessments of the treatments will be performed after treatment, on the 7th day, the 14th day, and the 28th day. All practitioners involved in the trial are trained and registered professionals. Acupuncture was performed by primary physicians with >5 years of experience at each center. A training program to standardize all manipulations and filling of a case report form (CRF) will be provided before the trial. Investigators will inform all patients about the possible inconveniences of the trial.

### Ma’s bamboo-based medicinal moxibustion group

The specific operations of Ma’s bamboo-based medicinal moxibustion group are as follows: (1) Preparation powder of Ma’s bamboo-based medicinal moxibustion: Wei Ling Xian (*Clematidis Radix Et Rhizoma*), Du Huo ( *Angelicae Pubescentis Radix*), Rou Gui (*Cinnamomi Cortex*), Xi Xin (*Asari Radix Et Rhizoma*), Chuan Xiong (Chuanxiong Rhizoma), Sang Ji Sheng (*Taxilli Herba*), and Gui Zhi (Ci*nnamomi Ramulus*) (250g each) will be mixed and powdered through a 300-mesh sieve and stored in a dark box for later use. (2) Preparation of medicinal wine of Ma’s bamboo-based medicinal moxibustion: Wei Ling Xian (*Clematidis Radix Et Rhizoma*), Ji Xue Ten (*Spatholobi Caulis*), Chuan Niu Xi (*Cyathulae Radix*), Xi Xin (*Asari Radix Et Rhizoma*), Du Huo (*Angelicae Pubescentis Radix*), Chuan Xiong (*Chuanxiong Rhizoma*), Sang Ji Sheng (*Taxilli Herba*), and Rou Gui (*Cinnamomi Cortex*) (200g each) will be placed in 21,000 mL liquor and spirits of 50° for 7 days for subsequent use. (3) Preparation of medicinal moxibustion tool: bamboo tube with an inner diameter of 5cm is taken with the stem nodes removed, and cut with a hacksaw according to the specification of 5×4cm (inner diameter × height). Then, with the removal of the bamboo bark on the surface, the edge of the bamboo tube is polished smooth and round to prepare a unique medicinal moxibustion tool. (4) Preparation of moxa cone: 3 g of moxa (Suzhou Medical Appliance Factory, Suzhou, Jiangsu, China) are made into several moxa-cone with moderate hardness (2.5 cm in height and 2 cm in diameter) for reserve. (5) Operation: 15g of medicinal powder and 20 ml of medicinal wine are mixed evenly, and the finished product is then placed into the medicinal moxibustion tool to press into the medicinal cake. Moxa cone will be placed on the compressed powder and ignited for preheating. The patients are informed to take the prone position with the moxibustion sites exposed. L1-L5Jia ji (EX-B2), Shenshu (BL23), Mingmen Point (GV4), and Yaoyangguan (GV3) are selected for moxibustion. The acupoint positioning is performed in accordance with the nomenclature and location of acupuncture points (GB/T 12346-2006), [19]. The therapist should ensure that the moxibustion site of the patient is continuously warm without burning pain. The moxa-cone are replaced after burning out, with a total of 3 cones, and the treatment is last for about 40min. The operation process of Ma’s bamboo-based medicinal moxibustion is presented in Fig. 3.

**Fig. 3 Fig3:**
[figure not shown]
The operation process of Ma’s bamboo-based medicinal moxibustion

### Acupuncture group

The selection of acupoints for the acupuncture group will follow according to the major acupuncture point prescription in *the Evidence-Based Guidelines of Clinical Practice with Acupuncture and Moxibustion Low Back Pain* [20], with positioning based on Nomenclature and Location of Acupuncture Points (GB/T 12346-2006) [19]. Each patient will be instructed to take the prone position. Disposable sterile needles of 0.30×40mm and 0.30×50mm (Suzhou Medical Appliance Co., Ltd., Suzhou, Jiangsu, China) will be used for the Shenshu (BL23), Dachangshu (BL25), Weizhong (BL40), L1-L5Jiaji (EX-B2), and Ashi points. The therapists will strictly follow the basic puncture methods and techniques in China’s acupuncture operating specifications for treatment [21, 22]. After insertion of the needle, basic lifting and twisting techniques will be performed until the needling sensation of de qi is achieved.

### Combined use of drugs

During the whole period of observation, it is suggested that the patients do not use drugs or other methods for the treatment of low back pain in LDH in addition to the experimental scheme. During the treatment period, if the patients take medication by themselves or use other methods of treatment due to aggravated symptoms and unbearable lumbar pain, they will be withdrawn from the trial. The clinicians will make the appropriate treatments according to the specific conditions of the patient until the symptoms are improved.

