Key inclusion and exclusion criteria	***Inclusion criteria*** Patients who meet all of the following criteria will be enrolled in the trial: (1) patients who meet the above diagnostic criteria and pathological classification, with the lesion located in L3–S1; (2) patients aged 18–65 years, males or females; (3) patients with the course of disease ≥6 months; (4) drug users with drug withdrawal for 4 weeks, and non-drug users with discontinued treatment for 2 weeks; (5) patients with 3 ≤VAS scores ≤6; (6) willingness to sign written informed consent. ***Exclusion criteria*** Patients who meet any of the following criteria will be excluded from the trial: (1) patients with acute onset of low back pain in lumbar disc herniation; (2) patients with low back pain caused by other causes; (3) patients with other diseases requiring combined treatment using anti-inflammatory and analgesic drugs; (4) patients during pregnancy,lactation or pregnancy preparation; (5) patients with rash, skin damage, ulcers or other infectious diseases at the waist; (6) patients with serious diseases of the heart, liver, kidney,blood system, etc.; (7) patients with mental disorders or communication disorders who could not cooperate; (8) patients with high fever and yin deficiency.
Study type	Multicentre prospective randomized trial
Date of first enrolment	11 November 2020
Target sample size	312
Recruitment status	Recruiting
Primary outcome(s)	Visual analog scale (VAS)
Key secondary outcomes	Oswestry disability index (ODI); modified Japanese Orthopaedic low back pain (M-JOA) score; serum β-endorphin (β-EP); serum substance P (SP)

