### Sample size calculation

The PASS software version 15.0 (NCSS, LLC. Kaysville, UT, USA.) was used to estimate the sample size. The trial is designed to determine the efficacy of Ma’s bamboo-based medicinal moxibustion therapy on low back pain in LDH and prove that its clinical efficacy is not inferior to normal acupuncture therapy. Therefore, we chose a non-inferiority trial design. According to the previous literature [8, 18] and the joint consideration of clinicians and statisticians, it is assumed that the standard deviation of VAS score reduction of patients using bamboo-based medicinal moxibustion is 2.0, the non-inferiority margin was set at 0.78, the significance level of the test is unilateral 0.05 and power of the test is 90%. According to the 1:1 grouping, the sample size required by each group was 140 cases, and the lost follow-up rate will be estimated at 10%. The final sample size of the treatment group and the control group was 156 cases respectively, and the total sample size was 312 cases.

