### Outcome measurements

#### Primary outcomes

##### Visual analog scale (VAS)

We will use the visual analog scale as the primary outcome measure [23]. VAS is one of the sensitive and reliable methods for pain measurement, which is used to evaluate the degree of low back pain. VAS scores ranged from 0 points to 10 points, which were described in detail as follows: 0: painless; less than 3 points: slight pain that can be tolerable; 4–6 points: pain to affect the sleep, which can be tolerated; 7–10 points: gradually intense pain, which is unbearable and affects appetite and sleep.

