### Concomitant care

From the time of participation in this study to the end of follow-up, it is recommended that patients do not take anti-inflammatory and analgesic drugs or any other non-drug therapy for low back pain, because this may affect the objective evaluation of the efficacy of Ma’s bamboo-based medicinal moxibustion therapy. However, if the patient needs to use other treatment methods other than the treatment plan of this study, patients can apply to the investigator to withdraw from the clinical trial, and any rights and interests of the patient will not be harmed.

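### Withdrawing patients who take other treatment for unbearable pain can lose outcome-linked VAS values, which may modestly raise the chance of false non-inferiority

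*Protocol article*

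**What the plan says.** **The rule.** Under Combined use of drugs, patients who during the treatment period medicate themselves or use another method "due to aggravated symptoms and unbearable lumbar pain, they will be withdrawn from the trial". The clinicians then treat them "until the symptoms are improved". Drop out criteria lists outcome-affecting other treatment as a reason for withdrawal. Concomitant care covers the time up to the end of follow-up: patients who need other treatment are not removed by rule, but "patients can apply to the investigator to withdraw from the clinical trial".

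**After withdrawal.** Adherence says that withdrawn cases are logged and contacted by telephone, or at home if needed. It does not say what is measured.

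**The outcome.** VAS is the primary outcome. It is taken at baseline and then "on the 7th day, the 14th day, and the 28th day" (Interventions). Entry requires "3 ≤VAS scores ≤6" (Table 1), and scores of 7-10 are described as "gradually intense pain, which is unbearable and affects appetite and sleep".

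**The analysis.** Statistical analysis promises intention to treat, with linear mixed effects models for missing data. Sample size calculation uses a margin of 0.78, SD 2.0 and one-sided 0.05, and "the lost follow-up rate will be estimated at 10" percent.

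**The concern.** The rule ends trial participation, not just study treatment, and the event that triggers it is plausibly failure on the primary outcome: the pain that leads to withdrawal is described with the same word as VAS 7-10, while everyone enters at 3-6. Patients and therapists are unblinded, so unequal take-up of other treatment is possible, though not shown.

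A linear mixed model gives valid results when the recorded values explain the loss. A patient whose pain flares on day 11 has only the baseline and day-7 values on record. The model predicts a day-14 VAS from those values that is too low. If this happens more often on moxibustion, the model understates how much worse moxibustion is. In a non-inferiority trial that error favours the claim being tested. An analysis plan can choose how to handle missing values, but it cannot recover a VAS that nobody measured.

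**Working it through.** **1. The plan's own figures.** 140 / (1 - 0.10) = 155.6, so 156 per arm reproduces. The 140 does not follow from one-sided 0.05: 2 × (1.645 + 1.282)² × 2.0² / 0.78² = 112.6, so 113. One-sided 0.025 gives 138.2, so 139. That is a separate matter; the 156 randomised per arm is used here.

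**2. No loss.** SE = 2.0 × √(2/156) = 0.2265. Non-inferiority is declared if estimate + 1.645 × SE < 0.78. At a true difference of 0.78 the error is 5%.

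**3. Effect of a shift.** If loss pulls the estimate down by b, the error is about Φ(-1.645 + b/SE).

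**4. Size of the shift (simulation).**
- From the document: 156 per arm, SD 2.0, margin 0.78, one-sided 0.05, entry VAS 3-6, 7 or more taken as unbearable.
- Assumed: baseline uniform on 3-6; normal change from baseline; mean acupuncture reduction 1.0-2.0 points; correlation 0.4-0.8 between values 7 days apart; 100%, 50% or 25% of patients at VAS 7 or more take other treatment (take-up). Mean change and arm difference grow linearly to day 14, then stay flat.
- Analysis: likelihood estimate using all values before withdrawal.

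Worked cell (crossing checked at day 11, reduction 1.0, correlation 0.6):

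| Take-up | Withdrawn, moxibustion vs acupuncture | Estimate | Formula in step 3 | Simulated error |
|---|---|---|---|---|
| 100% | 11.0% vs 6.6% | 0.722 | b = 0.058: Φ(-1.389) = 8.2% | 8.3% |
| 50% | 5.5% vs 3.3% | 0.754 | b = 0.026: Φ(-1.530) = 6.3% | 6.1% |
| 25% | 2.7% vs 1.7% | 0.766 | b = 0.014: Φ(-1.583) = 5.7% | 5.5% |

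False non-inferiority over all assumed reductions and correlations:

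| When pain crosses 7 | 100% | 50% | 25% |
|---|---|---|---|
| Day 11; day-14 VAS analysed | 6.2-9.0% | 5.3-6.6% | 4.9-5.6% |
| Day 4 or 11; day-14 VAS | 7.2-9.6% | 5.6-6.8% | 5.4-5.9% |
| Day 11 or 21; day-28 VAS | 6.9-9.3% | 5.5-6.6% | 5.3-5.8% |

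At full take-up the second row loses 11-19% against 9-14%, which exceeds the planned 10%, so it is an upper case. With a larger mean reduction of 3.0 (day 11, correlation 0.6) the errors are only 5.9% / 5.5% / 5.3%.

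**5. When there is no bias, or it reverses.** Loss explained by the day-7 VAS: error 4.9-5.3%, estimate 0.78. Truly equal arms: estimate 0.00. Moxibustion better by 0.5: estimated as 0.47-0.49, so the bias then runs against it.

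**6. What each remedy does, measured against the difference without other treatment.**
- Adding VAS taken after other treatment to the main analysis: 6-8% at full and 5-7% at half take-up if that treatment lowers VAS by 1 point; 10-17% and 7-10% if by 3 points (both assumed).
- Carrying forward the VAS recorded when other treatment starts: 3.9-4.9% and 4.4-5.2% (day 11); 4.0-6.7% and 4.4-6.2% (day 4 or 11); 1.3-3.4% and 2.7-4.3% at day 28, which is conservative.

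**The case against.** **The article is condensed.** What is recorded at withdrawal may be in the full protocol or case report form, and the flow chart and assessment schedule are not shown. This stands: a reader might infer that VAS is never taken after withdrawal, but the document shows only that no available text says it is. The rule itself is stated twice, however, and is not an omitted detail.

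**Intention to treat is not contradicted.** A reader might infer that withdrawn patients drop out of the analysis. The text does not say so, and values before withdrawal stay in the mixed model. What remains is a possible missing-not-at-random problem that works against the aim.

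**The effect is small and conditional.** This stands too. It needs moxibustion to be worse by the margin, more loss on moxibustion, worsening unseen at day 7 and substantial take-up. Entrants have chronic, non-acute pain and have already stopped other treatment, so take-up may be low.

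**The model leans towards the concern.** The VAS 7 trigger is inferred, because the rule is triggered by self-treatment and not by a score. Using the full SD of 2.0 as early as day 4 inflates early crossing, and the normal model gives negative VAS for 4-10% of day-14 values. These points argue for reading the upper ends of the ranges with reserve.

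**Concomitant care is voluntary.** Patients may leave, and follow-up cannot be compelled. Any fix must respect that.

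**Conclusion.** The concern holds in a limited form. The rule lets VAS values tied to the primary outcome go unmeasured, and the planned model may not repair that. At a true difference equal to the margin, with more loss on moxibustion, false non-inferiority is about 5-7% at half take-up or less, and hard to tell from 5% at a quarter. It reaches about 9-10% only with near-total take-up and small mean improvement. The estimated difference is 0.70-0.76 at full and 0.75-0.77 at half take-up, instead of 0.78. Take-up, mean reduction, correlation and the VAS 7 trigger are all assumptions.

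A reader might infer that the error rate doubles or worse. If withdrawal is tied to the day-14 change itself (no improvement, or worsening by 0.5 or 1 point) and other treatment brings no benefit, simulated errors are 8.2-11.7% at half and 10.0-17.7% at three-quarters take-up. The document does not support that model as the expected case. The mandatory rule covers the treatment period, and "All the treatments will be completed within 13 days", so withdrawal precedes the day-14 value. The stated trigger is unbearable pain, not lack of improvement.

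The direction is not fixed either: the document gives no ground for saying which arm will lose more. The point should be fixed because the remedy is cheap, not because the error is shown to be large.

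**What to change.** 1. In Drop out criteria and Combined use of drugs, state that other treatment for low back pain ends study treatment but not follow-up. Align Concomitant care, keeping the patient's right to withdraw consent.
2. Add one record when other treatment starts: VAS, date, type and reason, taken before that treatment where possible.
3. Have the blinded data collector record VAS at days 7, 14 and 28 for every randomised patient, using the contacts already planned under Adherence, and include these values in the intention-to-treat analysis.
4. Before database lock, fix a supporting analysis that counts other treatment for worsening pain as unfavourable, for example by carrying forward the VAS from item 2. Read non-inferiority with caution if it disagrees. Item 3 alone is not enough, because VAS after effective other treatment hides the worsening.

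**Cost.** An ethics-approved amendment during recruitment, one extra record and a VAS item on existing contacts. Telephone VAS is verbal, VAS after other treatment partly reflects that treatment, and values for patients already withdrawn may be lost. With equal arms, the supporting analysis has slightly less power: from about 97% to 95-96% (crossing at day 11), or from 96% to 93-94% at half and 90-92% at full take-up (day 4 or 11).
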